## Methods

### Study Design

This is an intention-to-treat, single-blind, parallel, 2-arm clustered randomized controlled trial study. We will collect data at baseline (T1) and measure outcomes after program completion (T2) and follow-up at 3 months (T3) and 6 months (T4) to test our hypotheses. We include a retention period of 6 months to determine whether fall risk, dynamic balance, PA, altered maladaptive FRA (FRA shifting), and negative self-perceptions of aging are maintained without ongoing intervention. This study is registered on ClinicalTrials.gov (NCT05778604).

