### Power Analysis and Sample Size

The sample size estimate was based on the primary outcomes of fall risk (CDC fall risk score) and PA (normalized MVPA) for aim 1 and the secondary outcome of FRA shifting (BBS score) for aim 2. The difference in the normalized mean MVPA between the PEER group (mean 3.67, SD 2.54) and the control group (mean 5.38, SD 2.68) and the difference in the fall risk score between the PEER group (mean 2.72, SD=3.23) and the control group (mean 2.21, SD=2.06) are considered markers of PA and fall risk, respectively. Considering a clinically relevant normalized difference in MVPA of 1.7 (SD 2.60) and a fall risk score difference of 0.50 (SD 2.56), the medium effect size Cohen *d*=0.25, intraclass correlation (ICC) of 0.8, and a significance level of are used for the calculation of the sample size. A sample size of 120 participants per arm is needed to reach 80% statistical power to detect the difference between the PEER and control groups on repeated measures of normalized MVPA. A sample size of 120 participants per arm is needed to reach 80% statistical power to detect the difference between the PEER and control groups on repeated measures of normalized MVPA.

In addition, the sample size was also based on the following: (1) at least 3 sites per arm; (2) an initial hypothesis that at least 10% (34/340) of the irrational, incongruent, and congruent FRA would shift to rational FRA after PEER completion; (3) an approximate study adherence rate of 80% [56], and (4) an estimated study dropout rate of approximately 40% (136/340) over time. Therefore, the sample size was increased from 120 to 170 per arm, resulting in a total of 340 participants. On the basis of our pilot study [26], we estimate that approximately 60% (204/340) of the low-income older adults will meet all inclusion and exclusion criteria and will be interested in participating in this study. We estimate that a minimum of 567 low-income older adults will be screened to identify 340 low-income older adults for enrollment, and approximately 240 low-income older adults (120 per arm) are needed to complete the study. Given the sample size of 120 per arm, a significance level of *P*=.05, and 80% power, considering a clinically relevant BBS mean score difference of 8 (SD 12), the effect size Cohen *d*=0.36 can be achieved to compare the intervention effect based on secondary outcomes.

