### Recruitment, Randomization, and Procedures

Research sites will be recruited through a partnership with local communities, personal contacts, referrals, and phone calls. The unit of randomization is an independent living senior community, which is defined as a company-owned facility with a design for low-income independent adults aged ≥55 years and without health care services provided on campus. Research sites will be selected based on the prespecified criteria, including the number of residents, geographic proximity (urban vs suburban), and ability to implement the intervention. We plan to recruit 6 sites (3 intervention sites and 3 control sites). Collectively, approximately 10 sites and 800 low-income individuals are available for screening, and we can add sites, as they are abundant in the area. The participating sites will be randomized to either the intervention or control group in a 1:1 ratio. RX (coinvestigator and statistician) will use a computerized pseudorandom number generator to determine the randomization order in advance. The project director (PD) will reveal the randomization of the sites before the study [57]. Following randomization, we will recruit participants using standard strategies, including placing flyers on information boards and participating in open-house sessions or health fairs for face-to-face recruitment. Participants will also be recruited from their units by email. We will screen participants by a phone call to determine their initial eligibility, and those eligible will be invited for the baseline assessment. The research staff will explain the study and complete the consent process. The PEER intervention sites will be required to select 6 to 7 volunteers called *peer coaches* (PCs) to lead the exercise group, and the PCs will be eligible if they report having a regular PA routine or having an educational background in health care; are aged >55 years; can read, write, and understand English and Spanish; and are committed to delivering the protocol for 8 weeks. JS (coinvestigator) and the principal investigator (PI) will provide two, 3-hour sessions to train the PCs in balance and strength training, safety in the exercise, and participant motivation in collaboration with a successful PC from our pilot study. Each PC will be matched to 8 to 10 low-income older adults in the PEER group according to the place of residence and will supervise low-income older adults in groups while they are engaged in group exercises. This procedure was successful in our pilot study.

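### The sample size section makes no numerical allowance for randomising six communities (3 v 3), so the stated 80% power at 120 per arm and the detectable d=0.36 are not shown for this design

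*Protocol article*

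**What the plan says.** Under Study Design the trial is a "single-blind, parallel, 2-arm clustered randomized controlled trial study". Under Recruitment, Randomization, and Procedures, "The unit of randomization is an independent living senior community", and the plan is six sites: "We plan to recruit 6 sites (3 intervention sites and 3 control sites". Allocation is by site: "The participating sites will be randomized to either the intervention or control group in a 1:1 ratio".

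Power Analysis and Sample Size states that "A sample size of 120 participants per arm is needed to reach 80% statistical power" for repeated measures of normalised MVPA, using d=0.25 and an "intraclass correlation (ICC) of 0.8". It names three differences in original units: MVPA 1.7 (SD 2.60), fall risk score 0.50 (SD 2.56) and BBS score 8 (SD 12). It adds that 120 per arm gives 80% power for d=0.36 on secondary outcomes. Among the further bases it lists "1) at least 3 sites per arm", but no number follows from that item. The rise from 120 to 170 per arm is tied to having 120 completers per arm.

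The recruitment section also says that "approximately 10 sites and 800 low-income individuals are available for screening, and we can add sites".

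**The concern.** When communities are randomised, residents of the same community tend to resemble each other, and the arm contrast is judged against variation between communities. With three per arm, only 6 − 2 = 4 degrees of freedom are available to estimate that variation. A calculation that counts 120 people per arm as independent misses both effects. The article prints a specific power figure, so this is not a detail left to a fuller document: the figure has to belong to the design described.

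Fall risk, a primary outcome, has the smallest planned difference. If power for the smaller planned effects is well below 80%, a null result on them could be misread as evidence of no effect.

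**Working it through.** **Inputs from the protocol article.** 3 v 3 sites; 120 completers per arm, so m = 120/3 = 40 per site; alpha 0.05 (two-sided assumed). Standardised effects: d=0.36 and d=0.25 as stated; fall risk 0.50/2.56 = 0.195; MVPA 1.7/2.60 = 0.65; BBS 8/12 = 0.67.

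**Assumption.** The site ICC is not given; 0.01, 0.02 and 0.05 are shown.

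**1. The plan's own figures, for independent people.** SE = √(2/120) = 0.129.
- d=0.36: 0.36/0.129 = 2.79, and 2.79 − 1.96 = 0.83, so power is 79.6%. The d=0.36 claim reproduces, with each participant counted as independent.
- The MVPA statement does not reproduce. Using n = 2(1.96 + 0.84)²/d², d=0.25 needs 252 per arm and 1.7/2.60 needs 37 per arm, not 120.
- The step from 120 to 170 leaves no margin for clustering: 120/170 = 71% is simply the completer fraction.

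**2. Could the 0.8 be the site ICC?** The design effect would be 1 + 39 × 0.8 = 32.2, leaving 240/32.2, or about 7 effective people in the whole trial. Neither reading of the 0.8 supports 80% power for 3 v 3 sites.

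**3. Site clustering, one unadjusted measurement.** Design effect = 1 + 39 × ICC = 1.39 / 1.78 / 2.95. Effective completers per arm = 120/design effect = 86 / 67 / 41. SE = √(2[ICC + (1 − ICC)/40]/3) = 0.152 / 0.172 / 0.222. Power is from the noncentral t on 4 df.

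| Effect | Independent | ICC 0, 4 df | ICC 0.01 | ICC 0.02 | ICC 0.05 |
|---|---|---|---|---|---|
| d=0.36 | 80% | 56% | 44% | 36% | 24% |
| d=0.25 | 49% | 32% | 25% | 20% | 14% |
| Fall risk, 0.195 SD | 33% | 22% | 17% | 14% | 11% |
| MVPA, 0.65 SD | 99.9% | 96% | 89% | 81% | 61% |
| BBS, 0.67 SD | 99.9% | 96% | 90% | 82% | 62% |

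The smallest effect detectable with 80% power is d = 0.57 / 0.65 / 0.83. With the design effect alone and no df penalty, power at d=0.36 is 66% / 55% / 37%.

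**4. Closer to the planned analysis.** Take the mean of three follow-ups adjusted for baseline, with within-person correlation 0.8 for every pair of visits. The variance factor is f = (1 + 2 × 0.8)/3 − 0.8² = 0.867 − 0.640 = 0.227. How far baseline also removes site variance is unknown, so there are two bounds:
- low, none removed: SE = √(2[ICC + f(1 − ICC)/40]/3) = 0.102 / 0.131 / 0.192;
- high, removed in the same proportion: SE = √f × the SE in step 3 = 0.072 / 0.082 / 0.106.

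| Effect | ICC 0.01 | ICC 0.02 | ICC 0.05 |
|---|---|---|---|
| d=0.36 | 75–95% | 55–90% | 30–72% |
| d=0.25 | 46–73% | 31–63% | 17–44% |
| Fall risk, 0.195 SD | 31–53% | 21–44% | 12–30% |

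For 120 independent people per arm the same analysis has SE = √(2 × 0.227/120) = 0.0615. Power is then above 99% at d=0.36, 98% at d=0.25 and 89% for fall risk.

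**5. More sites, same people.** At 5 v 5, 240 completers are 24 per site and the test has 8 df. At ICC 0.02, unadjusted, SE = √(2[0.02 + 0.98/24]/5) = 0.156. Power at d=0.36 is 53%, against 36% with 3 v 3.

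**The case against.** The best defence has four parts.

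- **Sites were considered.** The section lists a minimum of three sites per arm, and more can be added. This stands against saying that clustering was ignored. It does not supply a number.
- **The unadjusted figures are a worst case.** The plan is a mixed model on four measurements including baseline. This stands. On that analysis power at d=0.36 can reach 80% or more at ICC 0.01 or 0.02, provided baseline removes much of the site variance. At d=0.25 and for fall risk it stays below 80% across the assumed range.
- **Clustering is not the whole cause.** On one unadjusted measurement, power is only 49% at d=0.25 and 33% for fall risk with independent people. This also stands: only the d=0.36 row starts from 80%, and much of its fall comes from having 4 df (56% at ICC 0).
- **The site ICC is assumed.** True. But with one unadjusted measurement, the 4-df test gives less than 80% at d=0.36 even at ICC 0.

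A reader might infer that the trial could not detect any of its planned effects. The documents do not support that: two of the three differences named in original units, MVPA and BBS, keep about 80% or more up to ICC 0.02 even unadjusted. (Those differences do not match the stated d=0.25 and d=0.36, which is a separate matter.) A reader might also take 0.8 as the site ICC. The text ties it to repeated measures, though it does not name the level.

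**Conclusion.** The concern holds in this form: the 80% power at 120 per arm and the detectable d=0.36 are not shown for a design with three communities per arm, because nothing in the calculation accounts numerically for site. For site ICC 0.01 to 0.05, power at d=0.36 is 44% to 24% on one unadjusted measurement. On a baseline-adjusted mean of three follow-ups it lies between about 95% and 30%, depending on the ICC and on how much site variance baseline removes.

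The risk of misreading a null result applies to the smaller planned effects, fall risk above all. It does not extend to MVPA and BBS at low ICC. The sizes rest on an assumed site ICC, equal sites of 40 completers and, for the adjusted figures, a correlation of 0.8 that holds for every outcome. That the allowance is missing rests on none of these.

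**What to change.** Rewrite the power paragraph:

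1. Say what the 0.8 is and, if it is the within-person correlation, label it so.
2. State an assumed site ICC with a range, for example 0.01 to 0.05, and the expected completers per site.
3. Give power and minimum detectable effect for the planned baseline-adjusted repeated-measures analysis, with site clustering and (sites − 2) df, beside the figures without clustering. State what is assumed about baseline and site variance.

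This costs one paragraph and, for the smaller effects, a less favourable figure. No participant is added.

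Optionally, where site opening still allows, spread the same 340 people over more of the roughly 10 available sites. At 5 v 5 (34 enrolled per site) power at d=0.36 and ICC 0.02, unadjusted, rises from 36% to 53%: a gain, not a return to 80%. The cost is extra site set-up. The 6 to 7 peer coaches required at each intervention site would also have to be reconciled with about 34 participants per site, since one coach per 8 to 10 people implies about four. Keeping the requirement at five sites would mean 30 to 35 coaches rather than 18 to 21.

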Raw acceleration data from ActiGraph will be downloaded and converted to “.csv” files using ActiLife 6 Software (version 6.13.4; ActiGraph LLC). PA data will be processed using the R package *GGIR* (version 2.4-0). *GGIR* R package used to process multiday raw accelerometer data for PA research [103] includes (1) auto-calibration of acceleration signals according to local gravity [104], (2) detection of nonwear time, and (3) calculation of the average magnitude of dynamic acceleration corrected for gravity (ie, Euclidean Norm Minus One) over 5-second epochs and expressed in milli-gravitational units (mg) [105]. Nonwear time and sustained abnormally high accelerations will be imputed using the default settings [105]. The Euclidean Norm Minus One cut-off points will be used to estimate the total time spent in sedentary behavior, light intensity PA, and MVPA in participants.

For missing data treatment, the missing values will be imputed using the method of multiple imputations [106]. The maximum number of missing values within a scale will be based on the guidelines provided by the scale developers or based on a limit of 25% missing values. In the first analysis, all low-income older adults will be included according to their original group assignment [100]. Participants in the PEER group who completed at least 5 of the 8 group-based sessions will be included in the per-protocol analysis. Although every attempt will be made to ensure that low-income older adults complete all assessments, there may be some participant attrition over time. The missing data mechanism is assumed to be missing at random. The dropout patterns or missing data rates for the 2 arms will be examined to assess the differences. When possible, the models should be modified to account for relevant factors such as age, sex, general health perception, and the number of falls in the 6 months leading up to the baseline. To determine the impact of the PEER intervention during follow-up evaluations, the group-by-time interaction term will be incorporated into the model. Effect sizes (Cohen *d*) [107,108] will be calculated based on the estimated means and the pooled SD.

Aim 2 is to examine the effects of the intervention on FRA shifting and negative self-perceptions of aging.

The hypotheses are as follows:

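### The step from 120 to 170 per arm is said to rest on 80% adherence as well as 40% dropout, but it has no allowance for adherence and does not cover the dropout either

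*Protocol article*

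**What the plan says.** All the sizing figures are in the protocol article, Power Analysis and Sample Size. The starting point is "A sample size of 120 participants per arm is needed to reach 80% statistical power to detect the difference between the PEER and control groups". The outcome named for that claim is normalized moderate-to-vigorous physical activity (MVPA), measured repeatedly, with "the medium effect size Cohen *d*=0.25, intraclass correlation (ICC) of 0.8" given as inputs.

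Four further considerations follow: a minimum of three sites per arm, a hypothesis about the share of participants shifting quadrant, "an approximate study adherence rate of 80" per cent, and "an estimated study dropout rate of approximately 40% (136/340) over time". The conclusion drawn is "Therefore, the sample size was increased from 120 to 170 per arm, resulting in a total of 340 participants". The section then adds that "approximately 240 low-income older adults (120 per arm) are needed to complete the study".

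Study Design and Data Analysis plan an intention-to-treat analysis. In the first analysis "all low-income older adults will be included according to their original group assignment". A per-protocol analysis takes PEER participants with at least 5 of the 8 group sessions.

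The article does not define study adherence in the sample-size section. It also does not say whether the planning differences are effects under full adherence or effects averaged over everyone assigned.

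**The concern.** A reader of the sample-size section will take 170 per arm to have been enlarged for two separate losses: people who leave, and people who stay but do not take up the programme. These act differently. Dropout reduces the amount of data. Non-adherence among those who remain reduces the mean difference in an intention-to-treat comparison, and covering it takes a larger inflation, by the inverse square of the dilution. If only one of the two was used, the stated basis is wrong, and a reader cannot tell whether the 80% power refers to an effect that already includes non-adherence.

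The word itself is also in doubt. Elsewhere (Treatment Fidelity and Monitoring; Exercise Adherence) adherence means taking part in the intervention or exercising at home. In the sample-size list it is study adherence, placed directly before dropout, and could mean staying in the study.

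**Working it through.** **Inputs, all from Power Analysis and Sample Size:** 120 per arm for 80% power; 170 per arm enrolled; adherence 80%; dropout 40%; 120 per arm needed to complete; d = 0.36 quoted as detectable at 120 per arm for secondary outcomes. The significance level is 0.05, taken as two-sided (my assumption for the model tests).

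**1. Reproducing 170.**
- Observed ratio: 170/120 = 1.417.
- Dropout alone, multiplying: 120 x (1 + 0.40) = 168, which is close to 170.
- Dropout alone, dividing by the retained fraction: 120/0.60 = 200.
- A loss of 30%, which the section does not state: 120/0.70 = 171.4, also close to 170. The loss implied by 170 to 120 is 1 - 120/170 = 29%.
- Adherence and dropout together: 120/0.8/0.6 = 250 if non-adherers are simply replaced, or 120/0.8²/0.6 = 313 if the effect is diluted to 0.8.

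The figure is reproduced by dropout alone, using the multiplying form. No form that includes adherence comes near it.

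**2. Does 170 cover the stated dropout?** 170 x 0.60 = 102 per arm, or 204 in total. The section requires 120 per arm, or 240 in total. It does not.

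**3. Adherence read as retention.** 80% retention gives 170 x 0.80 = 136 per arm, while 40% dropout gives 102. The two cannot both hold, and neither equals 120.

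**4. Adherence read as intervention uptake.** Let k be the intention-to-treat effect as a fraction of the full-adherence effect. If 80% of people adhere and the others keep a fraction r of the benefit, k = 0.8 + 0.2r. Taking 80% power at 120 per arm at face value,

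power = Φ(k x (1.960 + 0.842) x √(n/120) - 1.960).

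| Effect kept by non-adherers | k | n = 120 | n = 102 |
|---|---|---|---|
| none | 0.80 | 61% | 54% |
| 25% | 0.85 | 66% | 59% |
| 50% | 0.90 | 71% | 64% |
| 75% | 0.95 | 76% | 69% |
| no dilution (target is already intention-to-treat) | 1.00 | 80% | 73% |

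First row at 120: Φ(0.8 x 2.802 - 1.960) = Φ(0.282) = 61.1%. Starting from d = 0.36 directly, power is 79.6% undiluted and 60.7% with k = 0.8. Holding 80% power under full dilution would need 120/0.64 = 188 completers per arm.

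**5. What the printed differences give** (two-sample comparison, 120 per arm, before and after k = 0.8):
- MVPA, 1.7/2.60, d = 0.65: 99.9%, then 98%.
- Fall risk, 0.50/2.56, d = 0.20: 33%, then 23%.
- d = 0.25 as stated: 49%, then 34%.

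With d = 0.25 and correlation 0.8, averaging two to four measures needs 214 to 226 per arm, a change score 101, and baseline adjustment 57 to 90. None of these gives 120. The 80% in step 4 is therefore the section's claim taken as given; among its own inputs only d = 0.36 matches it.

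**The case against.** The strongest reply is that the four considerations are not a formula. A minimum number of sites and a hypothesis about quadrant shifts are not inflation factors, so adherence need not be one either, and an article condenses the full calculation. That explains why no factor is shown. It does not rescue the sentence, which draws 170 as a consequence of the list and places two incompatible or unused rates in it.

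A reader might go further and infer that the trial's power is really 61%, and that this applies to every intention-to-treat comparison. The documents do not support that, for these reasons:
- The 61% needs four unstated assumptions: that 80% is a share of people rather than mean attendance (80% of 8 sessions is 6.4, above the per-protocol cut-off of 5); that non-adherers gain nothing; that the target is a full-adherence effect, although the article calls the differences clinically relevant and gives them as differences between group means; and that the non-adherent are among the completers rather than among the dropouts.
- On the printed MVPA difference, the outcome named in the power claim, the loss is trivial (99.9% to 98%).
- The completers are not the analysis set. The mixed model uses all available data from everyone assigned, with multiple imputation for missing values, so participants with partial data also contribute.

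A reader might also take 120 completers per arm as what the plan expects. The section says only that they are needed; its own dropout rate leaves fewer.

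These objections hold against a single power figure. They leave the failed step from 120 to 170 untouched.

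**Conclusion.** The stated derivation is wrong as written. Adherence is named as a basis for the increase to 170 but is not in the number, and 170 falls 18 completers per arm short of the requirement at the stated dropout (102 against 120). This part needs no assumption beyond the printed figures. If study adherence means retention, the section also contradicts itself.

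The effect on power is conditional. If adherence means intervention uptake and the stated 80% power is accepted, intention-to-treat power is between about 61% and 80% with 120 completers per arm, and between about 54% and 73% with 102. The lower ends rest on the four assumptions listed under the objection; the upper ends apply if the planning difference already averages over non-adherers. Both ranges leave out the randomization of six sites and any information from partly observed participants. They are not results of the printed MVPA or fall-risk inputs.

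**What to change.** In Power Analysis and Sample Size:

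1. Define study adherence. If it means retention, keep one loss figure in place of 80% and 40%.
2. If it means intervention uptake, choose one statement. Either the target differences are intention-to-treat effects, and adherence is removed from the reasons for the increase to 170; or they are full-adherence effects, and the diluted intention-to-treat power is printed as a range with the assumed effect in non-adherers.
3. Restate the expected completers at 170 enrolled under the dropout rate that is kept (102 per arm at 40%; 170 x 0.70 = 119 at 30%; 136 at 20%), and give the power at that number in place of the power at 120.

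The cost is a few sentences. Enrolment, procedures and analysis are unchanged. The stated power becomes less favourable if 40% dropout is kept or if the targets are full-adherence effects.

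### Forty percent dropout, 340 enrolled and 240 completers cannot all hold: at 40% dropout, 340 enrolled leaves 204 completers

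*Protocol article*

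**What the plan says.** All of the figures stand in the protocol article under Power Analysis and Sample Size.

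- Requirement: "A sample size of 120 participants per arm is needed to reach 80% statistical power to detect the difference" for the repeated MVPA measure. It is later put in terms of completion: "approximately 240 low-income older adults (120 per arm) are needed to complete the study".
- Expected loss: "an estimated study dropout rate of approximately 40% (136/340) over time".
- Enrolment: "Therefore, the sample size was increased from 120 to 170 per arm, resulting in a total of 340 participants".
- Screening, as a separate step: "a minimum of 567 low-income older adults will be screened to identify 340 low-income older adults for enrollment".

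The enrolment figure follows a list of four considerations: the number of sites per arm, an expected rate of shift in fall risk appraisal, an 80% adherence rate and the dropout rate. The article does not print the formula that takes 120 to 170. The same section closes with a statement for the secondary outcomes, that 120 per arm gives 80% power at Cohen d = 0.36.

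**The concern.** An allowance for dropout has one purpose: enough people must be enrolled that the required number remain after the expected loss. Here the enrolled number, the expected loss and the required number are all printed, and the first minus the second does not give the third. The section therefore fails on its own figures, without any outside assumption.

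Two things depend on it. The first is the number of completers that the team plans for, since a trial that retains exactly as many people as it expects would still miss its own target. The second is the pair of power statements, for the primary MVPA measure and for the secondary outcomes. Both are made for 120 per arm, and the plan's own dropout rate does not deliver that number.

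**Working it through.** **Inputs** (all from Power Analysis and Sample Size): 120 completers required per arm; dropout 40%, printed as 136/340; 170 enrolled per arm, 340 in total; 240 completers required in total; 567 screened; d = 0.36 at 80% power with significance level .05. The 1:1 allocation of sites is given under Recruitment, Randomization, and Procedures.

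**1. What 340 refers to.** With 60% eligible and interested, 340/0.6 = 566.7, which rounds to the stated 567. So 340 is the number enrolled after screening losses, and the 40% applies after enrolment.

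**2. Completers under the stated dropout.** 340 × (1 − 0.40) = 340 − 136 = 204, and 204/2 = 102 per arm. The shortfall is 240 − 204 = 36, and 36/240 = 15%.

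**3. Dropout that the enrolment figure can bear.** 1 − 240/340 = 29.4%.

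**4. Where 170 might come from.**

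| Route | Result per arm | Close to 170? |
|---|---|---|
| 120 × 1.4 (multiply up by 40%) | 168 | yes |
| 120/0.6 (divide by the 60% retained) | 200 | no |
| 120/0.7 (divide, with 30% dropout) | 171.4 | yes |
| 120/0.8 (adherence alone) | 150 | no |
| 120/(0.8 × 0.6) (adherence and dropout) | 250 | no |

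Two routes fit. One uses the stated 40% with the wrong operation. The other uses the right operation with a rate that the article does not state. The printed text cannot separate them.

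**5. Effect on the secondary-outcome power statement.** The plan's own figure is reproduced first. For two arms of n, two-sided alpha .05 and 80% power, the detectable standardized difference is about (1.960 + 0.842) × √(2/n).

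- n = 120: 2.802 × √(2/120) = 0.362. The exact t test gives 0.363. This matches the plan's 0.36.
- n = 102: 2.802 × √(2/102) = 0.392. The exact t test gives 0.394.
- Power at d = 0.36 with n = 102: 0.36 × √(102/2) − 1.960 = 2.571 − 1.960 = 0.611, and Φ(0.611) = 0.73. The exact t test gives 73% at either 0.36 or 0.363.

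So the plan's 0.36 is what a simple two-sample comparison of 120 against 120 can detect. With the completers that the stated dropout leaves, the figure becomes about 0.39. These calculations ignore clustering by site and count a dropout as contributing nothing.

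**The case against.** **The counts over 340 may be mechanical.** The article attaches 204/340 to the 60% who are eligible and interested, although that rate applies to the people screened. It also attaches 17/340 to a percentage of intervention sessions. The printed 136 may therefore be no more than 40% of 340 and not an independent figure. This is fair, but the conflict needs only the 40%. Nor does the printed 204/340 concede the shortfall, because it describes eligibility and not completion.

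**The analysis uses partial data.** Dropout accrues over time up to six months. The Data Analysis section specifies intention to treat, a mixed model that uses all available data, and multiple imputation, so a person lost after the second or third assessment still contributes. This stands as a limit on the power loss. It does not reconcile the figures, because the plan states its requirement as people who complete the study.

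**The loss is small or immaterial at the plan's own differences.** By the same t test, ignoring clustering, the plan's MVPA difference (1.7/2.60 = 0.65) and BBS difference (8/12 = 0.67) have more than 99% power at 102 per arm. The fall risk difference (0.50/2.56 = 0.20) has about 33% at 120 and 28% at 102. Moving from 120 to 102 changes neither picture. That stands, and it is why the size of this point is expressed only on the plan's d = 0.36 statement.

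**Stronger readings that a reader might infer.** One is that the authors multiplied by 1.4 when they should have divided by 0.6. No formula is printed and 120/0.7 fits as well, so that is a possibility and not a finding. Another is that the trial's power is 73%. That figure belongs to a single comparison at d = 0.36 for the secondary outcomes and not to the repeated-measures calculation for the primary outcomes. A third is that the power quoted for 120 per arm is wrong because of the dropout. Power given 120 is unaffected by this point; what is overstated is the expectation of having 120. Finally, the 80% adherence rate cannot be traced in any figure, but an article need not show how each input entered, so that is not evidence here.

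**Conclusion.** The inconsistency is real and rests on subtraction alone: with 340 enrolled and 40% dropout, 204 complete (102 per arm), against a stated need of 240. At least one of the three figures has to change, and 240 from 340 requires dropout of no more than 29.4%.

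The statistical consequence is modest and conditional. For the secondary-outcome statement, the detectable d moves from 0.36 to about 0.39, or power at 0.36 falls from about 80% to about 73%. This assumes a two-sample t test, no clustering allowance, and complete loss of information from dropouts. The primary-outcome claim of 80% power also presumes 120 per arm, but no recomputed power is attached to it here. Whether 120 per arm is itself adequate is a separate question on which this point does not depend.

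**What to change.** Keep 340 and do one of the following under Power Analysis and Sample Size.

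- **(a) Keep 40% dropout.** State that 204 participants (102 per arm) are expected to complete, against the target of 240. Restate the secondary-outcome figure as a detectable d of about 0.39 at 80% power, or about 73% power at d = 0.36, by two-sample t test before any clustering allowance. Add that partial data in the mixed model may reduce the loss, and that the primary-outcome statement of 80% power also presumes 120 per arm. Leave the 240 target in the text, since deleting it would hide the shortfall.
- **(b) Change the dropout assumption to about 29%**, if evidence supports that rate, and correct the count that goes with it. The figures 340 and 240 then agree.

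In either case, print the formula that takes 120 to 170. The cost is a few sentences and, under (a), one less favourable number. Neither option adds participants. Reaching 240 completers at 40% dropout would take 240/0.6 = 400 enrolled, but the correction does not require that step.
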